### Sample size calculation

Based on the results of other studies evaluating probiotic strains that will be used in the present study, we assume that the mean effect of intervention will be of a medium size. As the primary outcomes will be repeatedly measured and four groups of patients will be entering the trial, there will be an approximately 81% probability of correctly rejecting the null hypothesis of no difference between the study groups with a total of 116 patients.

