**Fig. 1 Fig1:**
[figure not shown]
Timeline of SANGUT STUDY visits. V0 – Screening visit; V1 – Baseline Visit; V2 – Visit 2; V3 – End of Study Visit

**Table 1 Tab1:** Schedule of study procedures

	Screening	Randomization	Intervention Period	End of the study
Visit Number	V0	V1	V2	V3
Visit time and Window	Day –7 to –1	Day 0	6 weeks ±3 days	12 weeks ±3 days
Informed consent	+			
Inclusion/exclusion criteria	+	+		
Somatic examination	+	+		
Neurological examination	+	+		
Socio-demographic characteristics	+			
Medical history	+			
Psychiatric history	+			
Depression symptoms severity	+	+	+	+
Stress level	+	+	+	+
Quality of life	+	+	+	+
Gastrointestinal symptoms	+	+	+	+
Dietary assessment	+	+	+	+
Physical activity	+	+	+	+
Anthropometric measures	+	+	+	+
Vital measures	+	+	+	+
Smoking status	+	+	+	+
Blood sample	+			+
Stool sample	+			+
Electroencephalography	+			+
Adverse events report		+	+	+

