### Data management and analysis plan

#### Data analysis principles

To evaluate the efficacy of the intervention on the well-being of patients, the following changes from the baseline (V1) to the end of the study (V3) will be determined as primary outcomes:
The severity of depression symptoms:
MADRS total scoreBDI total scoreThe severity of psychopathological impairment:
SCL-90 total scoreThe quality of life:
SF-36 total scoreStress levels:
PSS-10 total score

To evaluate the effect of the intervention on physiological parameters [79], the following changes will be determined as secondary outcomes:
In serum, from the screening (V0) to the end of the study (V3), levels of:
proinflammatory biomarkers: hs-CRP, Il-6, Il-1beta, and TNF-alphagluten sensitivity biomarkers: anti-TG2 IgG antibodies and anti-AGA IgG/IgA antibodiesintestinal permeability biomarkers: I-FABP/FABP-2 and LBPmetabolism biomarkers: total cholesterol, LDL cholesterol, HDL cholesterol, TG, glucose, and insulinHPA axis biomarker: cortisolliver function biomarkers: ALT and ASTIn stool, from the baseline (V1) to the end of the study (V3):
taxonomic and functional analysis of gut bacterial communitySCFAs levelsBrain activity, from the baseline (V1) to the end of the study (V3):
EEG analysisGastrointestinal symptoms, from the baseline (V1) to the end of the study (V3):
GSRS scale.

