To the best of our knowledge, this will be the first intervention study assessing the efficacy of both probiotic supplementation and a gluten-free diet and comparing the effect of both interventions and their combination in MDD patients. The protocol and the outline were developed by a multidisciplinary researcher team. The methodology employed in the study benefited greatly from our diverse set of knowledge, experience and perspectives. Considering the highly rigoristic selection criteria, the participant group is relatively large. Rigorous procedures established for this trial will be followed by well-trained researchers to ensure that research will be conducted in accordance with standards of best practice. The measurements listed above will be introduced to reduce the potential bias related to confounding variables (e.g. smoking, physical activity, and diet).

There may be some possible limitations in the design of the study:

First, the impossibility of blinding the diet is a factor that could affect assessment of both the participant and investigator. For this reason, the researcher evaluating the severity of symptoms will not be informed as to whether the patient will be allocated to the GFD or GD arm of intervention.

Second, the lack of motivation is a symptom commonly experienced by MDD patients and could contribute to the non-attendance at the study visits, incomplete implementation of the intervention, or failure to complete the intervention.

Third, patients in the GFD groups receiving dietary advice might try to introduce other changes in food consumption (e.g. reduce the food portion size and/or consume more vegetables and fruits). Therefore, health improvement may not be specific to the implemented gluten-free diet.

Finally, recall bias in self-reporting is another potential confounder of the study. However, dietary consultation and food intake assessment during the study period should minimize the likelihood of its occurrence.

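### The stated power of about 81% with 116 patients credits repeated measurement and is not tied to the declared primary outcome, a single V1-to-V3 change; 120 enrolled leaves room for only 4 losses

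*Protocol article*

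**What the plan says.** **Power.** Under Sample size calculation, the protocol article writes "we assume that the mean effect of intervention will be of a medium size". It then reasons: "As the primary outcomes will be repeatedly measured and four groups of patients will be entering the trial", and concludes with an "approximately 81% probability of correctly rejecting the null hypothesis of no difference between the study groups with a total of 116 patients". No numeric effect size, significance level, within-patient correlation, number of measurements, named test or dropout rate is given.

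**Primary outcome.** Under Data analysis principles, "the following changes from the baseline (V1) to the end of the study (V3) will be determined as primary outcomes". The list that follows has five scale totals (MADRS, BDI, SCL-90, SF-36, PSS-10). Each yields one change score per patient.

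**Visits.** Table 1 marks "Depression symptoms severity" at all four visits, V0 to V3. V0 (screening) and V1 (baseline, randomization) both precede treatment.

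**Analysis.** The Statistical analysis section lists ANOVA or Kruskal-Wallis for comparisons between groups, and repeated-measures or aligned rank-transform ANOVA for longitudinal data. It does not say which applies to the primary outcomes.

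**Numbers and losses.** Planned enrolment is 120, 30 per group. The Study population section discontinues patients for incomplete compliance with diet or probiotic and for missed visits, among other reasons. The Discussion says that low motivation could lead to missed visits and to "incomplete implementation of the intervention, or failure to complete the intervention".

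**The concern.** The power statement takes credit for repeated measurement. Averaging several correlated measurements per patient reduces variance and so raises power, but a two-point change score does not get that gain. If the 81% was calculated for a test that averages over visits, or for one that uses V2 as well, it describes a different comparison from the declared one.

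What is at stake is how a null result would be read. A trial described as having 81% power invites the conclusion that a medium effect was probably absent. If the declared comparison has materially lower power, that conclusion is not justified. The small gap between 116 and 120 adds to this, because the document itself provides for discontinuation and names reasons why patients might not finish.

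**Working it through.** **Inputs.** From the document: N = 116 for about 81% power, four groups, a medium effect, repeated measurement, four visits, primary outcome V1-to-V3 change, enrolment 120. Assumed because the document is silent: f = 0.25 for medium, alpha = 0.05, within-patient correlation r = 0.5 (range 0.3 to 0.7 shown). All powers are from the noncentral F distribution.

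**1. Reproducing the stated figure.** For the between-groups effect in a repeated-measures ANOVA with m visits:

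lambda = N × f² × m / (1 + (m − 1) × r), with df 3 and N − 4.

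With m = 4, r = 0.5 and N = 116: lambda = 116 × 0.0625 × 4 / 2.5 = 11.6, power **81.2%**. At N = 112 power is 79.6%, so 116 is the smallest multiple of 4 that reaches 80%. Both stated numbers match. At N = 116 and r = 0.5, three visits give 78.3% and two visits 72.9%.

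**2. Other settings that come close at N = 116.**

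| Setting | Power |
|---|---|
| Group-by-time interaction, 3 visits, partial-eta-type f: lambda = N × f² × (m − 1) = 14.5, df 6 and 224 | 81.6% |
| Between-groups effect, 2 visits, r = 0.25 | 81.2% |
| Between-groups effect, 3 visits, r = 0.45 | 80.6% |
| Interaction, raw f, r = 0.5: lambda = N × f² × m / (1 − r), 2 visits or more | 99.7% or more |

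For the three-visit interaction, 116 is again the smallest multiple of 4 reaching 80% (79.9% at 112). The first three settings are candidates and the last is not. A between-groups effect is a test of visit averages. The three-visit interaction is a 6-df test of any difference in pattern over V1, V2 and V3. None of the candidates is the V1-to-V3 change.

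**3. The declared outcome.** For a one-way four-group ANOVA on the change score, with f on the change-score SD: lambda = N × f², df 3 and N − 4.

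- N = 116: lambda = 7.25, power **59.0%**
- N = 120: lambda = 7.5, power **60.7%**
- 80% needs 180 patients (80.4%)
- The partial-eta interaction with two visits has the same lambda and df, so it also gives 59.0%

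If f = 0.25 is instead the V3 difference in raw-score SDs, the change-score SD is √(2(1 − r)) raw SDs, so lambda = N × f² / (2(1 − r)). At N = 116:

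| r | lambda | Power |
|---|---|---|
| 0.3 | 5.18 | 44% |
| 0.5 | 7.25 | 59% |
| 0.7 | 12.08 | 83% |

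Power of 81% is reached only at r of about 0.69.

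**4. Margin for losses.** 120 − 116 = 4 patients, and 4 / 120 = 3.3%. The document gives no loss rate, so the losses below are assumptions.

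| Loss from 120 | Completers | Four-visit model (step 1) | Four-group ANOVA on change, f on change SD |
|---|---|---|---|
| 10% | 108 | 78% | 55% |
| 15% | 102 | 75% | 53% |
| 20% | 96 | 72% | 50% |

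**The case against.** The sample size text names none of the inputs needed to reproduce it, so any reconstruction is inference. More than one setting fits, and the fact that 116 is the smallest N reaching 80% does not separate the four-visit average from the three-visit interaction. This stands. The document's phrase "correctly rejecting the null hypothesis of no difference between the study groups" favours the between-groups reading but does not prove it. A reader might infer that the authors certainly averaged in two pre-treatment visits. The text does not establish that, and on the three-visit reading that criticism falls away.

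A reader might also infer that the trial's power simply is 59%, with a false-negative risk near 40%. The document does not support that as a fact. It says only that the effect is medium, not on which scale or for which contrast, and the range of 44% to 83% extends above the stated 81%. Nor is a one-way ANOVA on change named as the primary test, and a different choice changes the answer. For example, a 2×2 main effect adjusted for the V1 score would have about 88% power at 120 (d = 0.5, r = 0.5). So the documents do not show that 120 patients are too few.

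On losses, the Discussion says that low motivation could contribute to non-completion. It does not forecast a rate, and the document does not say that discontinued patients leave the analysis. On the four-visit model, losses of 10% to 20% bring power down to 78% to 72%, which is a moderate reduction.

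What the objection does not remove is the mismatch. The one power figure offered rests on repeated measurement, and no candidate setting is the V1-to-V3 change that the same article makes primary.

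**Conclusion.** The point holds in a limited form. The arithmetic behind 81% and 116 can be reproduced and is not itself wrong; the figure is not tied to the declared primary outcome. On the inputs that reproduce it best (f = 0.25, alpha 0.05, r = 0.5), a four-group comparison of the V1-to-V3 change has about 59% power at 116 and 61% at 120. Those percentages depend on the scale of f, which is not stated, and on the choice of test. In raw-score SDs, the stated power would require a correlation near 0.7, which the article does not claim.

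The 3.3% margin is plain arithmetic and needs no assumption. It is thin beside the discontinuation rules and the article's own remarks on non-completion.

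**What to change.** Keep 120 patients and rewrite the sample size paragraph for the V1-to-V3 analysis actually planned. State the test, alpha, the numeric effect size and the SD it refers to, the assumed correlation, the number of visits used and the expected number of completers, and report the power that follows. If the test is a four-group ANOVA on change with f = 0.25 on the change-score SD, that means about 61% at 120 and about 50% at 96 completers (an assumed 20% loss). If another test is planned, give the figure for that test.

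The cost is one paragraph and, for the four-group comparison of change on these inputs, a less favourable stated power. No extra patients are needed.

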### Randomization

Randomization will be performed using a random sequence generator [44]. Patients will be randomized independently on antibody titers against gluten levels. The previously performed analyses will be used to check whether markers of abnormal response to gluten are useful in selecting the subgroup of patients who potentially benefit from a gluten-free diet.

Recruited individuals will be allocated into one of four groups:
Probiotic supplementation + gluten-free diet group (PRO-GFD; *n* = 30)Placebo supplementation + gluten-free diet group (PLA-GFD; *n* = 30)Probiotic supplementation + gluten-containing diet group (PRO-GD; *n* = 30)Placebo supplementation + gluten-containing diet group (PLA-GD; *n* = 30)

### Dietary interventions

#### Probiotic supplementation

The probiotic groups (PRO-GFD and PRO-GD) will receive one capsule containing the probiotic mixture powder (Sanprobi Stress; Sanprobi sp. z o.o., sp.k., Szczecin, Poland) in the amount of 3 × 10^9^ colony forming units (CFU) per day divided into two equal doses. The probiotic preparation will contain two bacteria strains: *Lactobacillus helveticus* Rosell®-52, *Bifidobacterium longum* Rosell®-175 and excipients: potato starch, magnesium stearate, and the capsule shell of hydroxypropyl methylcellulose. The placebo groups (PLA-GFD and PLA-GD) will receive the same capsule containing only the excipients, i.e. maize starch, maltodextrins, and the capsule shell. The placebo will be indistinguishable in color, smell, and taste from the probiotic formulation. Participants will be asked to consume the supplements before breakfast. Each of the study participants will be asked to collect the blister packs to evaluate compliance after the study.

#### Elimination diet

The patients in the GFD groups will follow the elimination diet containing no gluten. During the Baseline Visit (V1), participants will be educated about the rules of gluten-free diet restrictions and informed that the elimination diet is not a caloric restriction diet so the consumption of nutrients should not be changed. Information on the origins of gluten, the grains containing gluten, and highly processed food with gluten, will be received by all participants. They will be encouraged to consume natural, fresh foods and read the labels of food products in order to evaluate the gluten content. To avoid potential outcome bias resulting from a balanced diet and change in dietary habits, participants will be asked to follow their usual eating patterns, excluding gluten-containing products.

Before the intervention is implemented (between V0 and V1), patients will be asked to keep a diet diary (a 3-day food record). Changes and modifications in typical food consumption (based on the 3-day food record) during the consultation (at baseline, V1) will be proposed by a dietitian. Moreover, each participant will receive a list of products to be eliminated as well as a list of substitutes with the same taste, organoleptic properties, and nutritional values. A guide on the gluten-free diet and seven proposed menus for breakfast, lunch, dinner, and snacks will be given to each participant. The diet protocol will include only qualitative data, without the portion sizes, to keep the amount of food consumed at the current level. Patients will be educated about sticking to a diet by a dietitian during a consultation (visit V1).

### Data collection and methods

#### Tools

The following clinical/dietary information will be obtained:
Socio-demographic Data (a self-prepared questionnaire)Dietary habits: Food Frequency Questionnaire (FFQ-6) [45], a 3-day food recordPhysical activity: The International Physical Activity Questionnaire (IPAQ) [46]Smoking status by breath carbon monoxide levels in exhaled airVital signs: Heart rate (HR), blood pressure (RR), and core body temperatureAnthropometric measures: Weight, height, body mass index (BMI), waist-to-hip ratio, and body compositionThe severity of depressive symptoms: Montgomery-Asberg Depression Scale (MADRS) [47], and Beck’s Depression Inventory (BDI) [48]Psychological problems and symptoms of psychopathology: Symptom Checklist-90 Questionnaire (SCL-90) [49]Quality of life: Short Form (36) Health Survey (SF-36) [50]Gastrointestinal symptoms: Gastrointestinal Symptom Rating Scale (GSRS) [51]Subjective assessment of stress levels: Perceived Stress Scale (PSS-10) [52] and Childhood Trauma Questionnaire (CTQ) [53]

In the blood serum, we will evaluate markers of:
Gut barrier integrity: Intestinal fatty acid-binding protein (IFABP/FABP2), and lipopolysaccharide binding protein (LBP)Gluten sensitivity: Immunoglobulin G and immunoglobulin A anti-gliadin antibodies (anti-AGA IgG/IgA), and IgG anti-tissue transglutaminase (anti-tTG2)Inflammation: High-sensitivity C reactive protein (hs-CRP), tumor necrosis factor alpha (TNF-alpha), and interleukins IL-6 and IL-1 betaHPA axis activity: CortisolMetabolic indices: Total cholesterol, low density lipoprotein (LDL) cholesterol, high density lipoprotein (HDL) cholesterol, triglycerides (TG), glucose, and insulinLiver function: Alanine aminotransferase (ALT) and asparagine aminotransferase (AST)Excluded diseases: Hematopoietic system (peripheral blood morphology), thyroid diseases (thyroid stimulated hormone, TSH), diabetes (hemoglobin glycosylated, HbA1c), coeliac disease (total-IgA and IgA antibodies against tissue transglutaminase, anti-TG2), and allergy (total-IgE antibodies levels).

The following analyses will be conducted in the stool: gut microbiota (taxonomic and functional analysis) and concentrations of short-chain fatty acids (SCFAs).

Activity of the brain and its relationships with implemented interventions will be assessed with resting-state electroencephalography (EEG). After collecting raw EEG recordings, they will undergo mathematical analysis to obtain the quantitative parameters characterizing neural activity which can be evaluated with reference to applied experimental effects.

### Methods of assessment

#### Dietary assessment and diet adherence

Diet assessment and adherence to the protocol will be examined using the Food Frequency Questionnaire with six answers (FFQ-6) validated on a Polish population [45]. The FFQ questionnaire will be used to assess intake of 62 products (including the main gluten sources) divided into eight groups that are consumed in Poland. Respondents will have to select one out of six frequency categories: (1) never or almost never, (2) once a month or more rarely, (3) several times a month, (4) several times a week, (5) daily, and (6) several times a day. The FFQ questionnaire will be filled out by a clinical dietitian with experience in conducting nutritional interviews. Using the “Album of photographs of food products and dishes” [54], participants will determine the serving sizes of the consumed products. The amount of food intake which is not included in the aforementioned album will be determined using the ilewazy.pl website [55]. Patients will also be asked to complete a 3-day food record (including two weekdays and one weekend day) before the Baseline Visit (V1), and twice in the study period (first between 1 and 6 weeks from the implementation of the diet, and for the second time between 6 and 12 weeks from the implementation). Based on the food records, we will be able to estimate the nutritional value and assess the intake and percentage of consumed nutrients from the recommended amounts. According to the method from earlier studies (multiplying protein contained in gluten cereal by 0.8) [56, 57], gluten in patients’ diet will be estimated from the FFQ questionnaire and 3-day food records. Based on the FFQ results, alcohol consumption will also be estimated. A possible influence of other nutritional factors (energy value, nutrient intake) on the obtained results will be checked before and during the intervention based on dietary diaries.

#### Other lifestyle factors

Physical activity will be assessed using the International Physical Activity Questionnaire (IPAQ) which allows for expressing physical activity in the metabolic equivalent – MET-min/week [46]. The IPAQ estimates physical activity of different intensity levels (walking, moderate-intensity, and vigorous-intensity activities) during the last seven days. Based on the results, the responders are classified into one of three activity categories: ‘insufficient,’ ‘sufficient,’ or ‘high’. The level of physical activity is a potential confounder having an impact on gut microbiota composition [58, 59] and some biochemical parameters [60, 61]. Studies have also shown that excessive workouts affect gut permeability [59].

Smoking status will be evaluated by means of the Micro+Smokerlyzer (Bedfont Scientific Ltd., [name]) which is a quick method to analyze carboxyhemoglobin and carbon monoxide parts per million (ppm) levels in exhaled air. The monitor uses an electrochemical sensor, has a concentration range of 0 to 500 ppm, repeatability of less than ±5%, and an accuracy of 2 ppm. Evidence indicates that smoking dysregulates gut microbiome and leads to low-grade inflammation [62, 63].

#### Vital signs

Systolic and diastolic blood pressure and pulse rate will be measured using the standard digital meter in a seated position, after at least five minutes of rest, three times (in 1-min intervals) by placing the cuff on the left upper arm. The first measurement will be discarded. During the same visit, vital sings will be taken prior to blood sampling. Core body temperature will be monitored using a forehead digital thermometer. Abnormalities of clinical significance will be recorded as an adverse event.

#### Anthropometric measurement

The measurement of waist and hip circumferences (repeated twice at each visit) will be performed according to the World Health Organization (WHO) protocol [64]. Weight, body mass index (BMI), fat mass, muscle mass, and total body water will be measured using a segmental multifrequency bioimpedance analyzer (Tanita BC-601; Tanita Corp., Tokyo, Japan). All anthropometric data will be recorded after an overnight fast. Patients will be weighed while wearing light clothing and without metal objects (i.e. belt, jewelry). Participants will be asked to wear a similar amount of clothes on each visit. Evidence confirms a link between anthropometric parameters and other parameters assessed in our study [65–67]. Changes in anthropometric data will be considered as potential factors linked with metabolic parameters, inflammatory and gut permeability markers, gut microbiota composition, and physical and mental state. There is some weak evidence that gut microbiota may have an impact on body weight [68].

